## Abstract

**Background::**

The abdominal compartment syndrome (ACS) has been clearly identified as being one of the main causes of mortality after ruptured abdominal aortic aneurysm (rAAA). The ACS is defined as a sustained intra-abdominal pressure > 20 mm Hg associated with a new organ dysfunction or failure. A pilot study was conducted and found that the threshold of 3 among 8 selected criteria, we would predict an ACS occurrence with a 54% positive predictive value and a 92% negative predictive value. But a multicentric prospective study was clearly needed to confirm these results. The outcome of this new study is to assess the qualities of a predictive test on occurrence of the ACS after rAAA surgery.

**Methods::**

This is a 30 months prospective cohort study conducted in 12 centers and 165 patients will be included. All patients with a rAAA will be consecutively included, whatever the surgical treatment. At the end of surgery, all patients have an abdominal closure and a monitoring of intrabladder pressure will be established every 3 to 4 hours. Decompressive laparotomy will be indicated when ACS occurs. Follow-up period is 1 month. Eight pre- and per-operative criteria will be studied: anemia, hypotension, cardiac arrest, obesity, massive fluid resuscitation, transfusion, hypothermia, and acidosis.

**Discussion::**

In the literature, there is no recommendation about prophylactic decompression, but early decompressive laparotomy appears to improve survival. This study should make it possible to establish a predictive test, detect the ACS early, and consider a prophylactic decompression in the operating room.

**Trial registration::**

ClinicalTrials.gov, NCT02859662, Registered on 4 August 2016.

## Background

1

Despite improved management techniques of ruptured abdominal aortic aneurysm (rAAA), especially in vascular surgery, the perioperative mortality rate has not decreased these last years. The preoperative deaths are mainly due to uncontrolled bleeding and its consequences whereas the postoperative deaths are rather related to multiple organ failure that could be explained by a misdiagnosis or a delayed diagnosis of an occurring abdominal compartment syndrome (ACS).

The ACS has been clearly identified as being one of the main causes of mortality after rAAA.^[1,2]^ The ACS is defined as a sustained intra-abdominal pressure greater than 20 mm Hg associated with a new organ dysfunction or failure.^[3–7]^ Mainly risk factors known for intra-abdominal hypertension (IAH) (intra-abdominal pressure > 12 mm Hg) are diminished abdominal wall compliance, increased intra-abdominal contents, capillary leak or fluid resuscitation, others than coagulopathy, obesity, sepsis, shock, and hypotension.^[3]^

The mortality rate of ACS can reach 80% to 100% in the absence of treatment.^[8]^ Early detection and appropriate management of intra-abdominal hypertension and ACS have reduced their mortality.^[1]^ In addition to the medical management, decompressive laparotomy with temporary abdominal closure is the treatment of ACS.^[8–11]^ Importance of screening as well as early management has been demonstrated, but decompressive laparotomy has its own complications such as wall pain, evisceration or increase of infection, and could not be propose systematically.^[10,12–20]^

The identification of patients who are at high risk of ACS after surgical repair of rAAA in the operating room could allow detecting and managing earlier patients with an increase in intra-abdominal pressure and ACS. Several factors related to the occurrence of intra-abdominal hypertension and ACS has been identified in the literature.^[12,16,19]^ Ruptured abdominal aneurysm is one of the risk factors. Among the others risk factors identified during the last consensus conference, we selected 6 that could be diagnosed in the pre- and intraoperative period: systolic blood pressure, body mass index, massive fluid resuscitation, massive transfusion, hypothermia, and acidosis.^[3,7]^ We selected 2 additional criteria, anemia and cardiac arrest, more specific to rAAA. These 8 criteria are easily collected during the initial management, correspond to data of the usual management in these patients and easy to access even in the operating room. We chose to analyze both surgical techniques (open or endovascular) together because the prevalence of ACS in the literature is the same.^[10,12–17,21,22]^

Previously, we have conducted a retrospective pilot study in our center, which found that with the threshold of 3 among 8 selected pre- and intraoperative criteria, we would predict an ACS occurrence with a 54% positive predictive value and a 92% negative predictive value. The prevalence of ACS in our study was 17% and the mortality rate in the group of patients with an ACS was 37.5%.^[23]^ Nevertheless, it was a retrospective, monocentric study with a small population without systematically measure of intra-abdominal pressure and with posteriori diagnosis of ACS. A multicentric prospective study was clearly needed to confirm these results.

This study aims to specify a predictive test for the occurrence of an ACS after rAAA surgery. Early detection of the ACS could enable rapid management of patients and influence the mortality rate.

## Methods

2

### Study design

2.1

This is a French prospective cohort study on patients presented a rAAA. The number of patients to be included is 165. All patients with a rAAA will be consecutively included, whatever the surgical treatment, open surgery or endovascular surgery. The estimated duration of recruitment is 30 months.

The primary endpoint of the study is the occurrence of an ACS within 5 days after surgery. The predictive capacity of the occurrence of ACS will be measured by sensitivity, specificity, positive and negative likelihood ratio, positive and negative predictive value.

The secondary endpoints are the occurrence of an ACS within 5 days after surgery according to the type of surgical technique (open surgery or endovascular surgery), death within 30 days of intervention, and hospital stay (intensive care unit stay and total hospital stay).

The 8 pre- and per-operative criteria are:

(1)Anemia with hemoglobin < 10 g/dL(2)Persistent of a systolic blood pressure lower than 90 mm Hg(3)Cardiac arrest(4)Body mass index (BMI) > 30(5)Massive fluid resuscitation of more than 3500 mL/h for at least one hour(6)Transfusion ≥ 10 units of red blood cells since the beginning of the treatment(7)Hypothermia with a temperature of 33°C or below(8)Acidosis with a pH ≤ 7.2.

When a patient with an rAAA arrives at the emergency room, he can be included in the protocol. According to its clinical condition, information on the study will be given to him and nonobjection consent. If the patient is unable to give consent, his or her family will be contacted to confirm non opposition to data collection. The data collected are usual and the management of rAAA is the same. No further examination is necessary for the study because it is an observational prospective study.

At admission, the following data will be collected: age, gender, weight, height, BMI, medical, and surgical history. During the pre- and intraoperative period: pre- and perioperative criteria, abdominal closure conditions, type of intervention, surgical procedure, type of anesthesia, clamping time, blood loss, and anesthetic conditions.

At the end of surgery, all patients have an abdominal closure. Patients are transferred in intensive care unit for clinical and paraclinical monitoring. Normal intra-abdominal pressure, range between 0 to 5 mm Hg, is usually measured by intra bladder pressure and it is a reproducible and non-invasive method.^[21,24–26]^ So during the first days, monitoring of intra bladder pressure will be established. The measurements will be carried out every 3 to 4 hours according to the centers, during the critical clinical situation and/or if the results are greater than 12 mm Hg. The end of the critical period is defined by the cessation of sedation. If clinical worsening occurs, intra bladder pressure will be monitored and repeated every 3 to 4 hours again (Fig. 1). Decompressive laparotomy will be indicated when bladder pressure is > 20 mm Hg associated with a new organ failure. However, isolated elevation of bladder pressure could perform decompression laparotomy. Management of IAH and ACS will be done according to the usual practice and current recommendations.^[3–5,11,14]^ All patients will be monitored over a period of 30 days.

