**Figure 1 F1:**
[figure not shown]
Schedule of enrolment, interventions and assessments.

During the postoperative period, the following data will be collected: APACHE II and SOFA score,^[27,28]^ clinical and paraclinical follow-up, intra bladder pressure, hemodynamic stability, therapeutic used to control or decrease intra-abdominal pressure, complications (type, chronology, treatment), additional surgical procedure, secondary decompression laparotomy, condition of closure of the abdomen in case of decompression laparotomy.

At 1 month, follow-up visit and clinical examination is done. These data will be collected: 30 days mortality, intensive care stay, total hospital stay, cause of death, and clinical examination (Fig. 2).

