**Figure 2 F2:**
[figure not shown]
Study design.

A committee will be necessary for the a posteriori validation of the ACS diagnosis. It will consist of 2 persons (a surgeon and an intensivist) who are not aware of the patient's identity, surgeon's identity, and the value of the 8 criteria. For each patient, the data used to evaluate the diagnosis will be collected in a standardized file and presented to the member of the validation committee during specific sessions.

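### Decompression for raised bladder pressure alone can avert the primary endpoint, so these patients should be flagged and the accuracy estimates bounded

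*Protocol article*

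**What the plan says.** The Background of the protocol article gives a two-part definition: "The ACS is defined as a sustained intra-abdominal pressure greater than 20 mm Hg associated with a new organ dysfunction or failure". Section 2.1 (Study design) sets the outcome: "The primary endpoint of the study is the occurrence of an ACS within 5 days after surgery".

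The same section gives an indication for decompressive laparotomy that matches the definition (bladder pressure above 20 mm Hg together with new organ failure). It then adds an exception with no pressure threshold: "However, isolated elevation of bladder pressure could perform decompression laparotomy". The next sentence leaves treatment to the centres: "Management of IAH and ACS will be done according to the usual practice and current recommendations".

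Outcome assessment is retrospective: "A committee will be necessary for the a posteriori validation of the ACS diagnosis". The two committee members are blinded to the eight criteria. Postoperative data include bladder pressure, SOFA, "therapeutic used to control or decrease intra-abdominal pressure" and "secondary decompression laparotomy, condition of closure of the abdomen in case of decompression laparotomy". The indication for decompression is not in that list.

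Section 2.6 computes sensitivity, specificity, likelihood ratios and predictive values for the rule of at least 3 of 8 criteria. The Discussion part of the Abstract gives the purpose: detect ACS early and "consider a prophylactic decompression in the operating room".

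**The concern.** Decompression for pressure alone happens before the second half of the definition is met, and it can happen inside the 5-day window. If it works, organ dysfunction never appears and the patient is counted as free of ACS. The outcome then depends partly on how readily a centre decompresses.

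The direction depends on the test result of the averted case:

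- **Test-positive:** a true positive becomes a false positive. PPV, specificity and observed sensitivity fall.
- **Test-negative:** a false negative becomes a true negative. NPV and observed sensitivity rise, and specificity rises slightly.

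If averting is unrelated to the test result among would-be cases, true positives and false negatives shrink by the same factor. Sensitivity is then unchanged, but PPV is still too low and NPV too high. If the two are related, sensitivity, the measure used for sizing in section 2.7, moves as well. They could be related: the eight criteria are routine data (Background), and the article does not say that treating teams are unaware of them.

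This matters because a decision on prophylactic decompression in theatre needs the risk of ACS without early decompression. The primary analysis alone cannot show how far its figures depend on early treatment.

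**Working it through.** **The plan's own figure.** Section 2.7 uses sensitivity 0.75, precision 0.15, alpha 5% and prevalence 20%.

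- ACS cases: 1.96² × 0.75 × 0.25 / 0.15² = 32.01, rounded up to 33. Total: 33/0.20 = 165. Both figures reproduce.
- The half-width with 33 events is 0.148, so there is little slack. If 2, 4 or 8 of the 33 were averted (assumed counts), 1.96 × √(0.75 × 0.25/m) gives 0.152 (m = 31), 0.158 (m = 29) or 0.170 (m = 25).

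**Illustrative base table.** The Background gives pilot PPV 0.54, NPV 0.92 and prevalence 0.17.

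- Test-positive share: (0.17 − 0.08)/(0.54 − 0.08) = 0.196, or 32 of 165, leaving 133 test-negative.
- TP = 0.54 × 32 ≈ 17 and FP = 15. FN = 0.08 × 133 ≈ 11 and TN = 122.

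**Recounting.** Let n patients be decompressed early and recorded as non-ACS, k of them test-positive. Suppose a of the test-positive (0 ≤ a ≤ k) and b of the test-negative (0 ≤ b ≤ n − k) would have progressed. Then TP = 17 + a, FN = 11 + b, FP = 15 − a, TN = 122 − b.

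- PPV = (17 + a)/32 depends only on a, and NPV = (122 − b)/133 only on b. The primary analysis (0, 0) and the all-flagged analysis (k, n − k) therefore bound both.
- Sensitivity = (17 + a)/(28 + a + b) and specificity = (122 − b)/(137 − a − b) both rise with a and fall with b. So does LR+ = sensitivity/(1 − specificity); LR− does the reverse. Their bounds are the splits (k, 0) and (0, n − k).

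**Assumed n = 5, k = 2:**

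| Counted as events | TP/FN/FP/TN | Sens. | Spec. | PPV | NPV | LR+ | LR− |
|---|---|---|---|---|---|---|---|
| None (primary) | 17/11/15/122 | 0.61 | 0.89 | 0.53 | 0.92 | 5.5 | 0.44 |
| All 5 | 19/14/13/119 | 0.58 | 0.90 | 0.59 | 0.89 | 5.8 | 0.47 |
| Only the 2 test-positive | 19/11/13/122 | 0.63 | 0.90 | 0.59 | 0.92 | 6.6 | 0.41 |
| Only the 3 test-negative | 17/14/15/119 | 0.55 | 0.89 | 0.53 | 0.89 | 4.9 | 0.51 |

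The first two rows alone suggest 0.58-0.61 for sensitivity and 5.5-5.8 for LR+. The attainable ranges are 0.55-0.63 and 4.9-6.6.

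**Assumed n = 5, k = 3:** PPV 17/32 to 20/32 = 0.53-0.625; sensitivity 17/30 to 20/31 = 0.57-0.65; LR+ 5.1-7.2.

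**Sampling error on the base table.** Sensitivity: 0.607 ± 1.96 × √(0.607 × 0.393/28) = 0.43-0.79. For LR+, the log standard error is √(1/17 − 1/28 + 1/15 − 1/137) = 0.287, giving 3.2-9.7.

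**A second starting table.** Take the planned 33 ACS cases as 25 TP and 8 FN, with 14 FP and 118 TN (pilot-implied specificity 0.89). If 4 test-positive cases are averted, sensitivity goes from 25/33 = 0.76 to 21/29 = 0.72, PPV from 25/39 = 0.64 to 21/39 = 0.54, and specificity from 118/132 = 0.89 to 118/136 = 0.87. The mechanism does not depend on the base table; the size does.

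**The case against.** The strongest reply is that nothing here is misstated. Early decompression is usual care, the cohort is observational, and accuracy for ACS under usual care is a coherent target. A surgeon in theatre compares prophylaxis with postoperative care that includes rescue decompression, so that risk is relevant too, and section 3 leaves the prophylaxis question to a later randomised study. The classification rule and supplementary analyses may sit in a full protocol, analysis plan or committee charter that is not shown, and much of the flag could be derived from data already collected.

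Part of this stands. Care should not change, and ACS under usual care should remain the primary target. That averted cases are counted as non-events is inferred from the literal definition, because the article does not say how the committee will class them. The magnitude rests on assumptions, and the assumed 20% prevalence may already reflect centres that decompress early.

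It does not dispose of the point. The permission is stated in the article, and followed as written it lets treatment remove endpoint events. The stated use makes the risk without early decompression relevant alongside the usual-care figure. Adjudication can only judge what happened, and the logistic regression in section 2.6 predicts the same observed outcome. An indication that is never recorded cannot be supplied later by an analysis plan.

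**Conclusion.** The concern holds. As written, decompression for isolated raised pressure can turn a would-be ACS case into a non-event. For the intended use this pushes PPV down and NPV up, and moves sensitivity in a direction that depends on who is decompressed.

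The size cannot be established from the article: the number decompressed early, the share who would have progressed and the split by test result are all assumptions. With five such patients the illustrated shifts in sensitivity and LR+ are smaller than sampling error, but the confidence intervals do not cover this bias. The sample size is not shown to be wrong. This is an inexpensive improvement that should be made; it does not invalidate the design.

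**What to change.** Keep adjudicated ACS within 5 days as the primary endpoint and leave care unchanged. Then:

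1. Have the blinded committee flag any decompression within 5 days for raised bladder pressure without new organ dysfunction, using the recorded pressures, SOFA, decompression data and the indication.
2. After adjudication, tabulate flagged patients by test result and centre.
3. Pre-specify a sensitivity analysis counting all flagged patients as events. With the primary analysis it bounds PPV and NPV.
4. For sensitivity, specificity and likelihood ratios, take the bounds from two recalculations: only the test-positive flagged patients as events, then only the test-negative ones.

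The cost is one committee flag, possibly one added data item (the indication), one table, one sensitivity analysis and two recalculations. Readers will have four sets of estimates to interpret.

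The limits should be stated with the results. The all-flagged analysis may overstate accuracy, because it counts patients who would not have progressed and because clinicians may know the criteria. The bounds do not cover ACS averted by other pressure-lowering treatment. The centre visits described in section 3 may reduce differences between centres, but management still follows usual practice.

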**Figure 1 F1:**
[figure not shown]
Schedule of enrolment, interventions and assessments.

During the postoperative period, the following data will be collected: APACHE II and SOFA score,^[27,28]^ clinical and paraclinical follow-up, intra bladder pressure, hemodynamic stability, therapeutic used to control or decrease intra-abdominal pressure, complications (type, chronology, treatment), additional surgical procedure, secondary decompression laparotomy, condition of closure of the abdomen in case of decompression laparotomy.

At 1 month, follow-up visit and clinical examination is done. These data will be collected: 30 days mortality, intensive care stay, total hospital stay, cause of death, and clinical examination (Fig. 2).

**Figure 2 F2:**
[figure not shown]
Study design.

A committee will be necessary for the a posteriori validation of the ACS diagnosis. It will consist of 2 persons (a surgeon and an intensivist) who are not aware of the patient's identity, surgeon's identity, and the value of the 8 criteria. For each patient, the data used to evaluate the diagnosis will be collected in a standardized file and presented to the member of the validation committee during specific sessions.

### Objectives

2.2

The primary objective of the study is to assess the qualities of a predictive test on the occurrence of this syndrome after surgery of rAAA.

Secondary outcomes were to compare the test between surgical techniques (endovascular or open), 30 days mortality rate and the duration of hospitalization (intensive care unit stay and total hospital stay).

### Inclusion and exclusion criteria

2.3

Male or female patients to be enrolled in the study should meet the following inclusion criteria: age ≥ 18 years, to be hospitalized in participating hospitals, rAAA confirmed and operated.

Exclusion criteria are pregnancy, patients with bladder tumor or bladder surgery or trauma bladder can distort bladder pressure measurement, cystectomy, patients died before arrival in the operating room, patients died during surgery or within one hour of the initial surgical procedure, and patients whose abdominal closure at the end of the procedure is not possible.

### Data management

2.4

Data will be managed using the Clean Web business application, an electronic clinical trial management solution from Telemedicine Technology. This solution meets the requirements of BPC, ICH, 21 CFR Part 11 (FDA) control and ensures secure data hosting. It also allows for a thorough implementation of users’ access rights based on their profile on the study.

### Statistical analysis

2.6

The quantitative variables will be described using the mean and standard deviation, the median, and the minimum and maximum values. The qualitative variables will be described by the proportion and the percentage of each class.

As previously demonstrated, the test will be considered positive if the patient presents at least 3 criteria on the 8.^[23]^ Specificity, sensitivity, positive, and negative likelihood ratios, positive and negative predictive values with their confidence interval will be calculated for the new predictive test.

The comparison between surgical techniques used will be carried out with a Chi^2^ test or an exact Fisher test. A logistic regression carried out on sensitivity analysis will be done to build a predictive score and confirm the result.

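### ACS by surgical technique is a secondary endpoint in a non-randomised cohort, but the only comparison planned is an unadjusted chi-square or Fisher test, so a case-mix difference would pass into it uncorrected

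*Protocol article*

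**What the plan says.** Statistical analysis (2.6) fixes the method: "The comparison between surgical techniques used will be carried out with a Chi^2^ test or an exact Fisher test". Neither test can take a covariate. The next sentence contains the only regression in the article: "A logistic regression carried out on sensitivity analysis will be done to build a predictive score and confirm the result". It serves the predictive score and is not assigned to the technique comparison.

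Study design (2.1) describes how patients come to have one technique or the other: "All patients with a rAAA will be consecutively included, whatever the surgical treatment, open surgery or endovascular surgery". It describes usual management and adds: "No further examination is necessary for the study because it is an observational prospective study". Technique is therefore not randomised. The article does not say who chooses it or on what grounds.

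What is compared depends on the section. Study design lists as a secondary endpoint "the occurrence of an ACS within 5 days after surgery according to the type of surgical technique (open surgery or endovascular surgery". Objectives (2.2) says instead: "Secondary outcomes were to compare the test between surgical techniques (endovascular or open), 30 days mortality rate and the duration of hospitalization". The first is ACS incidence by technique; the second is the performance of the predictive test by technique.

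Background (1) pools the two techniques on a stated premise: "We chose to analyze both surgical techniques (open or endovascular) together because the prevalence of ACS in the literature is the same". The same section names shock and hypotension among the risk factors for intra-abdominal hypertension.

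**The concern.** The protocol treats persistent low systolic pressure and cardiac arrest as predictors of ACS, since both are among its eight criteria. In an emergency rupture it is plausible that the patient's state on arrival also bears on which technique is used. If so, the open and endovascular groups start with different ACS risks, and a 2x2 test cannot distinguish that from a difference due to technique.

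At stake is how the secondary endpoint is read. Depending on the direction of the imbalance, a real difference could be hidden or a spurious one produced. A reader may also carry the result over to the decision to pool the techniques.

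**Working it through.** **The plan's own figure.** Sample size calculation (2.7) uses sensitivity 0.75, precision 0.15 and alpha 5%: n = 1.96² × 0.75 × 0.25 / 0.15² = 32.01, rounded up to 33 ACS cases. At 20% prevalence, 33 / 0.20 = 165 patients. Both figures reproduce. The study is sized for sensitivity, not for the technique comparison.

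**Illustration A: one pre-operative factor, all inputs assumed.** ACS risk is 35% with and 12% without pre-operative hypotension, and is the same for both techniques within each stratum. Hypotension is present in 55% of open and 25% of endovascular patients.

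- Open: 0.55 × 0.35 + 0.45 × 0.12 = 0.2465
- Endovascular: 0.25 × 0.35 + 0.75 × 0.12 = 0.1775
- Crude difference: 0.069, with no technique effect. Swapping the two shares reverses the sign.

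**Illustration B: stratum risks from the pilot, case mix assumed.** Background gives a positive predictive value of 54% and a negative predictive value of 92%. ACS risk is then 54% in score-positive patients and 1 − 0.92 = 8% in score-negative patients. Some of the score's items can arise during surgery, so it only stands in for severity here. With no technique effect within a stratum, the rate in a group with score-positive share s is 0.54s + 0.08(1 − s).

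The rejection rate of the unadjusted two-sided 5% test is approximated by 1 − Φ((1.96·s0 − Δ)/s1) + Φ((−1.96·s0 − Δ)/s1). Here Δ is the crude difference, s0 the pooled standard error and s1 the unpooled one. The ranges cover 70:30 (115 and 50 patients) and 50:50 (82 and 83) splits of the 165. Both splits are assumed.

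| Score-positive shares | Crude ACS rates | Crude odds ratio | Test rejects in |
|---|---|---|---|
| 20% and 20% | 17.2% and 17.2% | 1.00 | 5% |
| 25% and 15% | 19.5% and 14.9% | 1.38 | about 10–12% |
| 30% and 10% | 21.8% and 12.6% | 1.93 | about 26–35% |
| 35% and 5% | 24.1% and 10.3% | 2.77 | about 54–65% |

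Worked row (30% and 10%, groups of 82 and 83): the pooled rate is (82 × 0.218 + 83 × 0.126)/165 = 0.172, s0 = 0.0587, s1 = 0.0584 and Δ = 0.092. Then (1.96 × 0.0587 − 0.092)/0.0584 = 0.396, and 1 − Φ(0.396) = 0.346; the second term is negligible.

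**Scale against sampling error.** With an even split and 20% ACS in both groups, the 95% half-width of the crude difference is 1.96 × √(0.20 × 0.80 × (1/82 + 1/83)) = 0.122, about 12 percentage points. A 7-point bias lies inside that, so the comparison is imprecise as well as open to confounding.

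**Room for a model.** With 33 expected events and about 10 events per term (a rule of thumb, not from the documents), about three terms are supportable: technique and two covariates.

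**The case against.** The strongest reply is that the article seeks no causal effect of technique. Its aim is a predictive test, and ACS by technique can be read as a simple breakdown, for which crude rates are legitimate. Under Objectives the thing compared is the test itself. A regression of ACS on technique does not compare sensitivity or specificity between groups, and hypotension and cardiac arrest are components of the test. The premise for pooling concerns prevalence, a crude quantity, so crude rates are its direct check. All of this stands. It is why the crude comparison should be kept and why test accuracy should be reported without this adjustment.

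A reader might infer that the treating team selects the technique and that the comparison therefore does reflect selection. The first part is a reasonable inference from the observational design, but no section states it. No section says that case mix differs, by how much or in which direction.

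A reader might also infer that the pre-operative values needed for adjustment are already available. Study design lists the eight criteria as pre- and per-operative together, so their timing relative to surgery is not shown to be recorded.

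Nor would adjustment isolate an effect of technique. Inclusion and exclusion criteria (2.3) removes patients who die during surgery or within an hour of it, and those whose abdomen cannot be closed. These events follow the choice of technique and may differ by technique; covariates do not repair that.

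Finally, covariates for a secondary analysis are often left to an analysis plan that is not shown. That would answer a complaint about silence. Here the article names the test and assigns its one regression to another purpose.

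**Conclusion.** The point holds in a limited form. For the endpoint of ACS by technique, the stated method leaves any difference in pre-operative severity uncorrected, in a cohort without randomised technique. If severity differs, a crude difference or its absence may reflect case mix.

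The size is unknown. Under the assumed inputs above, the spurious gap is about 5 to 14 percentage points, and a nominal 5% test rejects in about 10% to 65% of studies. With equal case mix there is no bias. These figures assume no technique effect within strata, and illustration B also assumes that the pilot's predictive values carry over.

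The documents do not support saying that the comparison is biased, that the article claims a causal effect, or that the crude test is wrong as a description. The issue concerns a secondary endpoint and leaves the primary accuracy analysis untouched.

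**What to change.** In Statistical analysis:

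- Keep the crude ACS rates by technique and the chi-square or Fisher result, labelled descriptive. They also check the equal-prevalence premise in Background.
- Add a penalised logistic regression of ACS within 5 days on technique with a few pre-specified pre-operative covariates, about three terms in all. Candidates are systolic pressure below 90 mm Hg and cardiac arrest, each before the start of surgery. Admission variables are an alternative; Study design already lists "the following data will be collected: age, gender, weight, height, BMI, medical, and surgical history".
- Do not adjust for intraoperative fluids, transfusion, temperature or pH, which technique may itself change.
- State that the comparison is observational, and that residual confounding and the exclusions occurring after the choice of technique remain.
- Report the accuracy of the predictive test by technique, as in Objectives, separately and without this adjustment.

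The cost is one or two sentences of analysis text, one field on the case report form recording whether hypotension or cardiac arrest preceded the start of surgery, and a slightly wider interval for the technique term. If admission variables alone are used, the timing field is not needed, but control for haemodynamic state is lost.
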